### 3.5 The intervention procedure

All enrolled patients are required to consume a light and easily digestible diet 1 day before the examination and begin fasting 6 h prior to the examination, with no liquids allowed 2 h before the procedure (27). For the participants of this study and their families, we will provide comprehensive information regarding the informed consent process. One hour before the commencement of the trial, staff will accurately fill in each patient's number on the top right corner of the basic information questionnaire based on the number of patients scheduled for screening that day, and strictly prepare the gastric formulation according to the specified drug ratio. Additionally, according to the prepared blind protocol, patients will be assigned to the corresponding groups based on their different numbers, and medication will be distributed 30 min before the examination (28). In control group A, the patients consumed only 50 ml of simethicone 600 mg in water, in experimental group B, the patients consumed 50 ml of pronase 20,000 u in water, in experimental group C, the patients consumed 50 ml of N-acetylcysteine 600 mg in water, and in experimental group D, the patients consumed 50 ml of simethicone 600 mg and 20,000 u of pronase mixed in water, and in experimental group E, the patients consumed 50 ml of simethicone 600 mg and N-acetylcysteine 600 mg. In experimental group F, patients drank 50 ml of simethicone dissolved in water 600 mg + 20,000 u pronase and 1 g of sodium bicarbonate solution.

After drinking the medication, patients will be professionally instructed by nurses “1–1” to perform position reversal training, including right side position, prone position, left side position, and flat position, and each position should be uniformly breathed for 10 times, and 5 consecutive position changes should be performed (29). In addition, we placed MP3 audio and animated videos in the examination waiting room, in the form of a Mandarin version and a dialect version (to accommodate patients with different literacy levels), with a duration of 4 min, which were used to instruct the patients in the correct operation of turning. Throughout the process, nurses will follow the instructions to ensure that the patient has a clear view of the mucosal background so that the physician can perform an accurate examination. Meanwhile, all patients will receive deep sedation with propofol at 1.5–2.5 mg/kg in the presence of a qualified anesthesiologist, administered at 5–7 min intervals. If the depth of sedation is insufficient, 0.5 mg/kg of propofol will be slowly pushed until proper sedation is achieved. During deep sedation, we will closely monitor the patient's vital signs, including pulse, oxygen saturation, heart rate, blood pressure, and other key indicators. In addition, all patients will receive 4–5 L/min of supplemental oxygen through an oxygen mask to ensure their comfort and safety during the examination.

During the examination, the patient was placed in the left lateral position with the head slightly tilted forward and the legs flexed. After the anesthesiologist confirmed that the patient had reached a state of deep sedation, the same senior endoscopist inserted the endoscope through the mouth. Under direct endoscopic visualization, the procedure began at the upper esophagus, sequentially examining the upper esophagus, lower esophagus, cardia, upper gastric body, lower gastric body, gastric antrum, gastric angle, and gastric fundus. Special emphasis was placed on performing narrow-band imaging (NBI) from the hypopharynx to observe the hypopharynx and esophagus, and 20 magnified gastroscopy and NBI images were captured separately (30). A researcher with a master's degree in nursing recorded the patient's vital signs and observational indicators during the examination. At the end of the examination, the image data obtained from the subjects were scored for gastric clarity by two experienced endoscopists (the reading physicians were unaware of the preoperative gastric preparation regimen the patients had received in this study). They also recorded the presence of any suspicious lesions and the pathological results of subsequent routine gastroscopy reviews. In case of disagreement in the assessment, a third endoscopist made the final decision. After the patient regained consciousness from anesthesia, they were asked to complete a feedback questionnaire regarding their satisfaction with the ME-NBI examination and were informed of post-examination precautions. The nursing researcher followed up with the patient via telephone or other mobile means the next day to inquire about any adverse events they might have experienced.

### 3.6 Outcomes and measurements

Patients participating in the trial underwent a baseline assessment conducted by a Master of Nursing researcher who was blinded to the group assignments. The baseline assessment data will encompass, but not be limited to, demographic factors such as age, gender, marital status, level of education, employment status, socioeconomic status, dietary habits, severity of illness, medical history, mental state and sleep patterns.

#### 3.6.1 Primary outcomes

The primary objective of the study is to compare the effects of different preoperative medication preparation regimens on the cleanliness of the gastric mucosa in individuals infected with Helicobacter pylori. To achieve this goal, we referred to the scoring criteria proposed by Kuo et al. (31), using the gastric mucosa cleanliness score as the primary outcome measure. The visibility of four parts of the stomach—namely the antrum, the lower body, the upper body, and the fundus—was scored separately. The scoring system ranges from 1 to 4 points, and the total score for each patient is calculated based on the visibility of their gastric mucosa. Two additional senior endoscopists independently scored the images of each patient. In cases of scoring discrepancies, a final consensus score was determined through joint consultation. The clarity of each image was assessed according to specific criteria. The classification criteria for gastric mucosal cleanliness are shown in Table 1.

**Table 1 T1:** Gastric mucosal clarity scale.

**Scale**	**Content**
Score 1	No adherent mucus and clear views;
Score 2	A thin coating of mucus that does not obscure views
Score 3	Gastric antrum, stomach body, fundus a little foam, blurred vision, need to wash with a small amount of water (< 30 ml);
Score 4	Almost all gastric mucosa has very thick mucus, blurred vision, need to wash with more water (>30 ml).

#### 3.6.2 Secondary outcomes

We also hypothesized that enhancing the clarity of the endoscopic field of view would facilitate early detection of gastric cancer in patients, increase patients' interest in early cancer screening, and enhance their understanding of amplification endoscopic narrowband imaging. This may ultimately lead to a higher detection rate of abnormal lesions, reduced anxiety, and improved patient experience. Therefore, we have established the following secondary endpoints. Secondary outcomes are shown in Table 2.

**Table 2 T2:** Secondary endpoint indicators.

**Item**	**Content**
Detection rate of early gastric cancer	Detection rate of early gastric cancer = number of pathologically confirmed cases/total number of endoscopy cases × 100%.
Polyp detection rate	Record the number, location and nature of polyps found during gastroscopy, and perform biopsy or excision for pathological examination.
Adverse reactions to taking the experimental drug	The patients' discomfort reactions, such as nausea, vomiting, abdominal pain, bloating, throat discomfort, etc. from oral drug solution to the end of the gastroscopy were recorded, and their frequency and severity were measured.
Gastric mucosal irrigation times	In the process of gastroscopy, when there is foamy mucous in the gastric mucosa of the patient, to observe and clear the gastric mucosa, the gastric mucosa should be rinsed with distilled water for about 30 ml each time.
Endoscopic time	Refers to the time required for the gastroscope to enter the oral piriform fossa at the entrance of the esophagus to the exit of the gastroscope at the end of the examination, in seconds (s), and excludes the time for biopsy.
Microscopic lesion detection rate	The number, location, and nature of lesions < 5 mm in diameter found during gastroscopy were recorded and biopsied or excised for pathological examination.
Willingness to re-examine	Willingness to check again if needed.
Preoperative anxiety	Preoperative anxiety was assessed using a self-rating scale of 0 to 10 points (measured by self-rated sleep quality before surgery [where 0 indicates very poor sleep quality and 10 indicates the same sleep quality as usual].

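### The adverse-reaction endpoint stops at the end of the gastroscopy, so symptoms that begin or are first felt after waking fall outside it, although the protocol already asks about adverse events the next day

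*Protocol article*

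**What the plan says.** Four places in the protocol article bear on this point.

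- **Section 3.6.2, Table 2.** The row on reactions to the study drug covers "discomfort reactions, such as nausea, vomiting, abdominal pain, bloating, throat discomfort, etc". Reactions "from oral drug solution to the end of the gastroscopy were recorded", and how often they occur and how severe they are is also measured. The window therefore opens with the drink and closes when the gastroscopy ends.
- **Section 3.5, timing and sedation.** The plan states that "medication will be distributed 30 min before the examination" and that "all patients will receive deep sedation with propofol". The order of steps is explicit: "After the anesthesiologist confirmed that the patient had reached a state of deep sedation, the same senior endoscopist inserted the endoscope through the mouth".
- **Section 3.5, after the examination.** "After the patient regained consciousness from anesthesia, they were asked to complete a feedback questionnaire regarding their satisfaction with the ME-NBI examination". The nursing researcher then "followed up with the patient via telephone or other mobile means the next day to inquire about any adverse events they might have experienced".
- **Section 3.7.** Data are to be recorded on a standard case report form at the appointment and on the day of the gastroscopy. The following day is not mentioned.

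The abstract lists the incidence of adverse reactions as a secondary endpoint without giving a window.

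**The concern.** Of the symptoms that Table 2 names, only vomiting is readily seen by staff. The others are known mainly because the patient reports them. The last part of the Table 2 window is spent under deep sedation, when the patient cannot notice or grade such symptoms, and the window closes before the plan has the patient awake again. The protocol does ask about adverse events the next day, but no row of Table 2 uses the answers and section 3.7 does not provide for recording them.

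Section 2 gives assessment of safety as one purpose of the additional measures. The Discussion hopes that a better regimen will reduce adverse reactions. The Introduction says that more work is needed on the safety of N-acetylcysteine in different populations. If the six regimens differ in symptoms that appear or are first noticed after the patient wakes, the endpoint as written cannot show it.

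**Working it through.** The point concerns an observation window. The plan states no figure to reproduce, and the check is a comparison of timelines.

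**Sequence of events, from section 3.5:**

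1. The solution is taken about 30 minutes before the examination. The patient is awake and does position-change training.
2. Deep sedation is induced in all patients.
3. The scope is inserted once deep sedation is confirmed, and the examination follows.
4. The gastroscopy ends. **The Table 2 window closes here.**
5. The patient regains consciousness and completes a questionnaire about satisfaction.
6. The next day, the patient is asked about adverse events.

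**Where a reaction falls:**

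| Onset of the reaction | Inside the Table 2 window? | When it can come to light |
|---|---|---|
| Between the drink and sedation | Yes | At once, or later by recall |
| During the examination, visible to staff (such as vomiting) | Yes | By observation |
| During sedation, not visible (such as nausea or pain) | Cannot be dated to the window; first felt after waking | Only after waking |
| After waking | No | Only after waking, including the next-day contact |

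The last two rows are the gap. Step 6 could supply this information, but Table 2 does not use that contact and section 3.7 does not list it.

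**What is inferred.** No sentence gives the patient's state at scope withdrawal. That the patient is still sedated follows from the order of steps 4 and 5, and section 3.5 describes no lightening of sedation beforehand. The point does not depend on the exact minute of waking: a reaction that begins after the gastroscopy ends is outside the window in either case.

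**The case against.** The strongest case for the plan is that the window is a deliberate choice about attribution. The Table 2 row concerns reactions to the study drug. After the examination, throat discomfort, bloating, nausea and abdominal pain can also come from the scope, a biopsy or the propofol. A window that stops at the end of the gastroscopy limits that mixing. On this reading the next-day contact is general safety follow-up beside a narrower tolerability endpoint, which is coherent.

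Much of this stands, and it argues against simply stretching one pooled endpoint to the next day. Randomisation balances the background symptoms between arms on average but does not stop them from diluting a drug difference. An illustration with assumed rates (none is in the documents), 44 patients per arm, two-sided 0.05, unpooled normal approximation:

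- Drug reactions of 5% against 25%: the standard error is √[(0.05×0.95 + 0.25×0.75)/44] = 0.0731, so z = 0.20/0.0731 = 2.74 and power is Φ(2.74 − 1.96) ≈ 78%.
- Add an independent 30% background: the rates become 1 − 0.95×0.70 = 33.5% and 1 − 0.75×0.70 = 47.5%. The standard error is √[(0.335×0.665 + 0.475×0.525)/44] = 0.1036, so z = 0.14/0.1036 = 1.35 and power is Φ(1.35 − 1.96) ≈ 27%.

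The objection does not remove the gap. It shows that later symptoms should be reported as a separate period. Nor can the gap be put down to an analysis plan that is not shown, because the article itself fixes the window and separately describes the later enquiry.

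**Conclusion.** The point holds as a mismatch between the endpoint's window and the follow-up that the protocol already describes. It is minor to moderate: one secondary safety endpoint is affected, and neither the sample size nor the primary analysis depends on it. The number of reactions missed cannot be stated, because the documents give neither rates nor onset times. The conclusion rests on the order of events in section 3.5 and on reading Table 2 literally.

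A reader might infer three stronger claims, which the documents do not support:

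- **That only symptoms voiced in the roughly 30 minutes before sedation can count.** Table 2 limits when a reaction occurs, not when it is reported. Nausea felt before sedation and described the next day is still inside the window, and vomiting during the examination can be observed.
- **That the next-day information is thrown away.** No sentence says so. It lies outside the defined endpoint and may still be reported as general safety data.
- **That the loss can be measured from the length of the window or the size of the arms.** A share of clock time is not a share of events, and the article says only that contact is made the next day. A confidence bound based on 44 patients would be the same for any window.

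**What to change.** 1. In Table 2, keep the present window as the first period.
2. Add a second prespecified period, from the end of the gastroscopy to the next-day contact.
3. At that contact, use the same symptom and severity checklist as on the day of the examination, and also ask by recall about symptoms felt before sedation. Assign each symptom to a period by its onset. Count a symptom first felt after waking in the second period.
4. Report each period and the total by arm.
5. Name the next-day contact in section 3.7 as a data-collection point with its own entry on the case report form.

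The cost is a few lines of wording and a checklist for a contact that already takes place. It needs no additional visit or patient and no change to treatment. The downside is that some second-period events will be due to sedation or endoscopy and not to the drink. The two periods should therefore be shown separately and not only pooled, with the first period kept as the cleaner comparison of the drugs.

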## 2 Objective

This study employs a single-center randomized controlled trial design, aiming to investigate whether the combined use of multiple defoaming agents and mucolytic agents, including simethicone, pronase, N-acetylcysteine, and sodium bicarbonate, prior to magnifying endoscopy with narrow-band imaging, can significantly enhance the clarity of the gastric mucosa in patients infected with *H. pylori*. Additionally, we have incorporated several observational metrics into the protocol to assess the safety of the procedure and the effectiveness of reducing the operation time.

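### Table 2 subtracts biopsy time but not excision time from endoscopic time, so any excision at the index examination can lengthen the measured time in regimens that reveal more lesions

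*Protocol article*

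**What the plan says.** Table 2 (section 3.6.2) starts endoscopic time at the oesophageal entrance and runs it "to the exit of the gastroscope at the end of the examination". It is recorded "in seconds (s), and excludes the time for biopsy". Nothing else is subtracted.

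Two other rows of the table say what happens to lesions that are found. For polyps, the plan is to record them "and perform biopsy or excision for pathological examination". Lesions under 5 mm "found during gastroscopy were recorded and biopsied or excised for pathological examination".

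The text introducing the table says of a clearer view: "This may ultimately lead to a higher detection rate of abnormal lesions". Section 2 adds, as a further purpose beside the primary one, to "assess the safety of the procedure and the effectiveness of reducing the operation time". Section 3.8 reports operation time as mean and SD and compares the groups by one-way ANOVA with least-significant-difference pairwise tests. It states no adjustment for excision. I take operation time there and endoscopic time in Table 2 to be the same outcome.

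**The concern.** By excluding biopsy, the plan accepts that tissue work prompted by a finding is not examination time. Excision is the same kind of time, and the table names it twice as the alternative to biopsy, yet the exclusion covers only one of the two. Two patients with the same small polyp and the same inspection would get different times if one polyp is sampled and the other is removed before withdrawal.

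The discrepancy need not be balanced across groups. Excision happens after the study drug is taken and depends on a lesion being seen, and the trial hopes a better regimen will make that more frequent. Randomisation therefore does not even it out. At stake is whether a difference in endoscopic time can be read as time saved on inspection and rinsing, or whether part of that saving is hidden by removal of extra lesions.

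**Working it through.** **The plan's own figures.** The documents state no expected value, difference or SD for endoscopic time, so there is no figure to reproduce for this outcome. The sample size in section 3.3.2 (40 per group, 40 × 1.1 = 44 with 10% dropout, 44 × 6 = 264) rests on the clarity score and does not bear on this point.

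**Bias formula.** Write measured time as T = I + E·d. Here I is time for inspection and rinsing, E is 1 if an excision is done before withdrawal and 0 otherwise, and d is its duration, taken as equal in all groups. Between two regimens, difference in mean T = difference in mean I + Δp × d, where Δp is the difference in the share of patients with such an excision. The second term is the bias. Its sign follows from the protocol's own hypothesis: if Δp is positive for the better regimen, that regimen's time is lengthened.

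**Size.** All inputs are assumed; none is in the documents.

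| Δp | d = 60 s | d = 120 s | d = 300 s |
|---|---|---|---|
| 0 (excision always deferred) | 0 s | 0 s | 0 s |
| 5 points | 3 s | 6 s | 15 s |
| 10 points | 6 s | 12 s | 30 s |

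With 44 per group, 5 to 10 points is 0.05 × 44 = 2.2 to 0.10 × 44 = 4.4 patients.

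**What a shift of this size could do.** Assume an SD of 120 s, 40 evaluable patients per group and a two-sided 0.05 pairwise test. The standard error of a difference is 120 × √(2/40) = 26.8 s, and power ≈ Φ(net difference / 26.8 − 1.96). For a true saving of 60 s:

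- no bias: Φ(60/26.8 − 1.96) = 0.61
- 6 s bias (net 54 s): 0.52
- 12 s bias (net 48 s): 0.43
- 30 s bias (net 30 s): 0.20

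For a true saving of 90 s, power is 0.92 without bias, 0.83 with 12 s and 0.61 with 30 s.

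**Added spread.** Suppose excision rates are equal, 10% of patients have an excision and each takes 180 s. The excision term then has SD 180 × √(0.10 × 0.90) = 54 s. If it is independent of inspection time, it combines in quadrature with the assumed 120 s: √(120² + 54²) = 132 s, about 10% more.

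**The case against.** The strongest objection is that the documents never place excision inside the timed interval. Table 2 says lesions are found during gastroscopy; it does not say when they are removed. Section 3.5 describes insertion, sequential inspection and image capture without mentioning biopsy or excision, and it refers to pathology from later routine gastroscopy reviews. A reader might infer that every excision is on the clock and that the time objective is therefore judged against the best regimen. The text does not support that. Section 3.5 does not move all excision to a later session either, so the question stays open.

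A second objection is that biopsy may be meant loosely, covering any tissue taken for pathology. That is possible in a condensed article. But the table itself sets biopsy and excision side by side as alternatives, so the wording needs clarifying even if this was the intention.

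Third, the magnitude is wholly assumed. With an SD of 120 s and 44 per group, the standard error of a difference is 120 × √(2/44) ≈ 26 s, so most of the 3 to 30 s range lies below one standard error. The extra spread is likewise modest, about 10% of the SD and not a further 54 s on top. Both criticisms stand.

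Fourth, subtracting excision does not separate time from lesion yield. Closer inspection, magnification and photography of a detected lesion also take time and remain in the measure. This stands too, and it limits what the fix can claim.

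**Conclusion.** The point holds as a gap in an explicit exclusion rule. Read literally, Table 2 counts any excision done before withdrawal at the index examination and subtracts a biopsy of a similar lesion. If such excisions occur, and if better views raise detection as the protocol expects, the effect lengthens measured time in the better-visualising regimens.

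Its size cannot be derived from the documents. It is about 3 to 30 s under the assumed 5 to 10 points and 60 to 300 s, and zero if excision is always deferred. It should not be presented as an established bias against the best regimen. This is a minor matter for one secondary endpoint; the primary clarity score and the sample size are unaffected.

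**What to change.** Reword the endoscopic time row of Table 2 so that the time for all tissue sampling and removal, biopsy and excision alike, is excluded. Use one clock rule for both: pause when the tissue procedure starts and resume when it ends.

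The cost is one phrase. Subtracting biopsy time already requires pausing the clock, so no new equipment or assessment is needed, and nothing in how lesions are managed changes. The report should say that extra inspection time on detected lesions is still included, so the endpoint is not wholly independent of lesion yield.

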**Methods:**

This study is a prospective, randomized, single-blind, single-center trial. The subjects are patients who require magnifying endoscopy combined with narrow-band imaging and have evidence of *H. pylori* infection (a non-invasive diagnostic ^13^C urea breath test was used to examine the study subjects). These patients will be randomly assigned to the control group (Group A) and the experimental groups (Groups B, C, D, E, and F). Each group will consist of 44 patients, with a total of 264 patients expected to be enrolled. The core content of the drug preparation regimen for each group is as follows: Group A (control group) will take 10 ml of simethicone before the examination; Group B (experimental group) will take 20,000 units of pronase before the examination; Group C (experimental group) will take 600 mg of N-acetylcysteine before the examination; Group D (experimental group) will take 10 ml of simethicone +20,000 units of pronase before the examination; Group E (experimental group) will take 10 ml of simethicone + 600 mg of N-acetylcysteine before the examination; Group F (experimental group) will take 10 ml of simethicone + 20,000 units of pronase + 1 g of sodium bicarbonate before the examination. All group medications will be dissolved in 50 ml of warm water at 20–40°C. All patients will fast for ≥6 h and abstain from drinking for 2 h before the examination. The primary endpoint is the gastric mucosa cleanliness score. Secondary endpoints include the early detection rate of gastric cancer, polyp detection rate, adenoma detection rate, procedure time, number of irrigations, patient medication compliance, preoperative anxiety, incidence of adverse reactions, overall patient satisfaction, and willingness to undergo the examination again.

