### 3.2 Blinding

Due to the nature of the intervention, all participants and endoscopists involved in the study were blinded to ensure the authenticity and objectivity of the data. The endoscopic procedures were performed by a single endoscopist with over 1000 ME-NBI procedures per year, and the quality of acquired images was analyzed and evaluated by two gastroscopy experts with ≥10 years of experience (with more than 500 cases reviewed). Initial baseline data collection will commence, with two other well-trained researchers (blinded to the groups) responsible for data collection. The investigator responsible for implementing the intervention will not be involved in the data collection process.

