## 4 Discussion

To the best of our knowledge, this study will be the first to explore the effect of different gastric mucosal preparation protocols on the clarity of gastric mucosa in gastric cancer risk groups in endoscopy, and the success of this randomized controlled trial will help the clinical staff to establish a more complete set of gastric mucosal preparation protocols to improve the early detection rate of gastric cancer in gastric cancer risk groups. According to the Kyoto Global Consensus Report on Gastritis (32), the self-cleaning ability of the gastric mucosa is weakened in *H. pylori*—positive patients, and the surface of the gastric body tends to be covered with more whitish and turbid mucus, so that more turbid mucus is retained in the stomachs of *H. pylori*—positive patients compared with that of healthy individuals. As a result, conventional preparation protocols are unable to optimize their preoperative preparation, and the existing means of repeated rinsing during gastroscopy, although it can solve this problem to a certain extent, has the problems of increasing the length of the examination and aggravating the patient's postoperative reactions, etc. Therefore, we hope that this study will find a useful preparation protocol through scientific exploration to improve clarity in the endoscopic field of view and to reduce the patient's Preoperative anxiety and adverse reactions.

Based on evidence-based evidence, this study designed a multi-group experimental protocol under the same experimental conditions for different drugs (33–37)—all of which are relatively effective in improving gastric mucosal clarity in previous experiments. We expect to use this experimental design to identify protocols to improve mucosal clarity and thus detection rates during endoscopy. We sincerely hope that this experiment will achieve such a goal.

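### The secondary endpoint called preoperative anxiety rates sleep before the examination, which a drink taken 30 minutes beforehand cannot change, so it cannot show an effect of the regimens

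*Protocol article*

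**What the plan says.** The abstract counts preoperative anxiety among the secondary endpoints, in a list that ends "patient medication compliance, preoperative anxiety, incidence of adverse reactions, overall patient satisfaction, and willingness to undergo the examination again". Table 2 in section 3.6.2 defines it as a 0 to 10 self-rating, "measured by self-rated sleep quality before surgery", with the anchors "where 0 indicates very poor sleep quality and 10 indicates the same sleep quality as usual". The text above Table 2 gives the rationale: a clearer endoscopic field may in the end lower anxiety, and the secondary endpoints are set up for that reason. The Discussion hopes that the trial will find a preparation "to reduce the patient's Preoperative anxiety and adverse reactions".

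On timing, section 3.5 states that "medication will be distributed 30 min before the examination". What comes next is described in the same section: "After drinking the medication, patients will be professionally instructed by nurses" in a series of position changes, followed by propofol sedation and the examination. Section 3.6 places "mental state and sleep patterns" among the baseline variables, and section 3.8 lists mental state and sleep again among the baseline data to be described.

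**The concern.** An endpoint can inform a comparison of regimens only if the regimen has had a chance to act on it. Sleep before a procedure, judged against the patient's usual sleep, belongs to a period that ends before the drink is taken. Compared between arms, such an item tests whether randomisation balanced the groups and says nothing about the drugs.

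The label adds to the problem. The row carries the name anxiety, contains no anxiety question, and gives its highest score to the patient who slept normally. A results table showing a higher preoperative anxiety score in one arm would in fact be reporting better sleep there.

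What is at stake is a patient-benefit statement. The Discussion already looks forward to less preoperative anxiety, and a nominally significant difference on this item could be cited for it although the design cannot support it.

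**Working it through.** The document gives no figure for this endpoint, so there is none to reproduce. The check sets the order of events against what is measured.

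1. **What is rated.** Table 2: self-rated sleep quality before the procedure, from 0 (very poor) to 10 (as usual). There is no anxiety item.
2. **When exposure starts.** Section 3.5: the drink is given 30 minutes before the examination.
3. **What lies between.** Section 3.5: nurse-led position changes, then deep sedation, then insertion of the endoscope. No interval for sleep is described. The comparison with usual sleep also points to an ordinary sleep period, which cannot fall within those 30 minutes.
4. **Consequence.** The rated sleep precedes the drug in every arm, so the expected drug effect on it is zero for all six groups.
5. **The stated mechanism.** Section 3.6.2 runs from a clearer view to reduced anxiety. The view exists only once the examination has begun. This path is closed to a rating of the time before the procedure, whether the patient is asked before or after drinking.
6. **Other routes to a difference.** Section 3.2 says that "all participants and endoscopists involved in the study were blinded". If blinding holds, knowledge of allocation does not explain a difference either. If the question is put after the drink, taste or discomfort could colour the answer. That would be reporting bias, not a change in sleep.
7. **Baseline duplication.** Sections 3.6 and 3.8 already treat sleep and mental state as baseline, so the protocol uses pre-examination sleep both as a baseline characteristic and as an outcome.

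One side calculation shows what a test of this item would deliver. Inputs: six groups of 44 (abstract), α = 0.05 (section 3.3.2), and one-way analysis of variance under the general rule for continuous variables in section 3.8, since no test is named for this item. With a true effect of zero and no reporting bias, the probability of a significant overall result equals α, that is 5%. A simulation of 40,000 trials with normal data gave 4.9%. Power therefore equals the false-positive rate, and a larger sample would not raise it.

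**The case against.** The strongest reply is that the protocol does not say when the rating is taken and does not mention the night before. Table 2 says only that the sleep precedes the procedure, and section 3.7 allows data collection at the appointment and on the day of the examination. This stands: that the sleep is over before dosing is an inference, though a close one, from the 30-minute interval and the comparison with usual sleep.

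A reader might go further and infer that every difference between arms must be chance. The documents do not support that. A rating given after the drink could carry reporting bias, and section 3.8.2 itself recognises that participants may discuss their drugs. The supportable statement is that a difference would not be a drug effect.

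A reader might also infer a large false-positive risk from unadjusted pairwise testing across the six arms. Section 3.8 names the least significant difference method only for operation time and mucosal cleanliness, and assigns no such comparisons to this item. No figure of that kind belongs here.

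Three further points have some force. Both anchors are printed, so a careful reader can recover the direction of the scale; the main defect is the name. The Discussion states a hope and not a claim. The rationale in section 3.6.2 speaks of reduced anxiety in general, so part of the mismatch is one of labelling. None of this lets the item respond to the regimen.

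**Conclusion.** The point holds. As defined, the endpoint measures sleep before the examination, is named anxiety, and cannot be altered by a drink taken 30 minutes ahead or by a view obtained later. The true drug effect on it is zero, so a difference between arms would reflect chance or reporting bias.

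The conclusion rests on one assumption: that the sleep being rated ended before the drink was taken. No section contradicts this, and the sequence in section 3.5 leaves no room for the alternative. The point does not depend on a detail left to a fuller document, because the article itself states the measure, its anchors and the dosing time.

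The reach is limited. One of ten secondary endpoints in the abstract, and one of eight rows in Table 2, is affected. The primary outcome, the sample size and the safety data are not. It should be corrected because the item is tied to a benefit that the authors hope to report.

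**What to change.** - Rename the item sleep quality before the examination, keep the anchors, and report it descriptively by arm with the other baseline variables in sections 3.6 and 3.8.
- Remove it from Table 2 and from the secondary endpoints in the abstract.
- Delete from the Discussion the hope that the regimens will reduce preoperative anxiety. The part on adverse reactions can stay.
- Let the satisfaction questionnaire carry the patient-experience question. Section 3.5 places it after recovery from anaesthesia, and the abstract already lists satisfaction as a secondary endpoint. Willingness to be examined again may also help, but Table 2 gives no time for its collection, so it should not be described as a post-recovery measure unless that is confirmed.

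No new data are needed and none are lost. The cost is one nominal secondary endpoint and a minor amendment to the protocol and the registry entry. Because the trial is registered and ethics-approved, this is a formal change and more than an edit of wording.
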